### Clinical Study Monitoring and Data Management

The Mayosi Collaborative Clinical Trials Unit at the University of Cape Town, South Africa, and the Hatter Cardiovascular Institute at the University College London, UK, will oversee the trial.

## Discussion

In the RIC-AFRICA study, we intend to investigate the role of RIC as a cardioprotective strategy in patients presenting with STEMI in sub-Saharan Africa. RIC, an endogenous phenomenon achieved by using a blood pressure cuff that is simply inflated and deflated for four 5-min cycles, activates many neuro-hormonal prosurvival signalling pathways that mediate cardioprotection and preservation of left ventricular function in many small and large animal studies [19–22]. Although the actual mechanisms through which RIC exerts myocardial protection from a remotely conditioned arm remains unclear, there are a number of small proof-of-concept clinical studies that have reported benefits of RIC improving myocardial salvage after acute myocardial infarction [8, 23]. Unfortunately, the translation of RIC into clinical practice has been faced with many challenges and obstacles with negative benefits in myocardial ischaemia/refusion injury post-cardiac surgery [24, 25]. In the recent large CONDI-2/ERIC-PPCI trial, RIC was unable to improve clinical outcomes in low-risk, uncomplicated STEMI patients recruited in high-income countries that were optimally treated by PPCI [11]. The CONDI-2/ERIC-PPCI trial recruited mainly a low-risk patient population as evidenced by the following: (i) the low cardiac mortality rate of 2.7% at 12 months; (ii) 96% of the cohort having presented without symptoms or signs of heart failure (Killip class I); (iii) the median acute MI size assessed by cardiac MRI in the first week following PPCI was relatively small, with a median MI size of 17% of left ventricular mass; (iv) the total acute myocardial ischaemia time was short with a median symptom onset to PPCI time of only 3 h; and finally, (v) the prevalence of cardiovascular risk factors were relatively low with 40% of patients having a history of hypertension, and only 10% having medically treated diabetes [13]. The benefit of RIC in higher-risk MI patients with greater comorbidities, larger infarct sizes, and longer total ischaemic times remains unknown.

The RIC-AFRICA study is particularly timely as the burden and mortality rates following STEMI experienced in low-and middle-income countries in sub-Saharan Africa are on the rise despite a decline noted globally [2, 3]. Other factors contributing to the observed worse outcomes in STEMI patients in sub-Saharan Africa include the following: (i) inadequate access to hospital facilities, especially in rural areas, resulting in prolonged transfer times to facilities where thrombolytic treatment is available [26]; (ii) the increased prevalence of cardiovascular risk factors such as hypertension (in up to 60% of patients) and diabetes (in up to 40% of patients), which remains undiagnosed and untreated in many people [26]; (iii) sub-optimal use and compliance of secondary preventative guideline-directed medical therapy at discharge post-STEMI; and (iv) high total acute myocardial ischaemia times with delayed presentations (> 6 h of chest pain onset) in nearly 70% of patients, confirming a higher-risk population [1].

Preliminary evidence on the safety, feasibility, and potential cardioprotective efficacy of RIC in STEMI patients treated by thrombolysis have already been demonstrated in the previously published phase 2, multi-centre, randomized controlled ERIC-LYSIS trial in the Island of Mauritius in which RIC initiated prior to thrombolysis reduced MI size as measured by a 32% reduction in 24-h area-under-the-curve serum cardiac biomarkers [23]. However, as recently discussed [12], there remains a need for a prospectively designed, randomized, sham-controlled clinical trial to determine whether RIC can improve clinical outcomes in high-risk patient groups.

Despite RIC failing to improve clinical outcomes in low-risk STEMI patients undergoing modern reperfusion therapy with primary PCI [11], the cardioprotective efficacy of RIC in higher-risk STEMI patients treated by thrombolysis in low-and middle-income countries where PPCI is not widely available remains largely unknown and potentially an attractive, more efficacious, low-cost, and non-invasive therapeutic solution.

In summary, the RIC-AFRICA trial will determine whether the simple, low-cost, non-invasive intervention of RIC can improve clinical outcomes in higher-risk STEMI patients treated by thrombolysis.

## Data Availability

As this is an announcement paper, no original data has been generated.

## Appendix

**Table 1. Tab1:** Definition of study endpoints according to the 2017 cardiovascular and stroke endpoint definitions for clinical trials [17]

Pre-discharge heart failure	I. New or worsening symptoms of heart failure (dyspnoea, decreased exercise tolerance, fatigue, or symptoms of worsened end-organ perfusion or volume overload) II. Objective clinical evidence of heart failure and fluid retention (such as pulmonary crepitations/crackles, raised JVP, S3 gallop, peripheral oedema, increasing abdominal distension/ ascites, or rapid weight gain thought to be related to fluid retention) III. Radiological evidence of pulmonary congestion/ oedema IV. Increased cardiac biomarkers (such as BNP > 500 pg/mL or NT-proBNP > 2,000 pg/mL) V. The initiation of intravenous or the significant augmentation of oral loop diuretic therapy
Heart failure hospitalization at 30 days	I. An admission ≥ 24 h II. A diagnosis of heart failure made by the treating clinician III. The initiation of intravenous or the significant augmentation of oral loop diuretic therapy
Non-fatal myocardial infarction	Acute re-infarction MI that occurs in the first 28 days after the index admission for STEMI, defined by [18]: I. Recurrent ischaemic symptoms II. New ST segment deviation in at least two contiguous leads III. A ≥ 20% increase between an immediate cTn value taken at re-admission and a subsequent cTn value taken 3–6 h later, exceeding the 99th percentile upper range limit
Transient ischaemic attack	A transient episode of focal neurological dysfunction caused by brain, spinal cord or retinal ischemia, without acute infarction
Stroke	An acute episode of focal or global neurological dysfunction caused by brain, spinal cord, or retinal vascular injury as a result of haemorrhage or infarction
Heart failure without hospitalization	An event that meets the clinical criteria for heart failure but does not meet the length-of-hospital stay, i.e. an admission < 24 h

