### Study Endpoints

#### Primary Endpoint

For the purpose of this trial, all endpoints were consistent with the 2017 cardiovascular and stroke endpoint definitions for clinical trials consensus document [17].

The primary composite endpoints of the study will be all-cause death and early post-MI heart failure. The latter is defined as (a) pre-discharge (in-hospital) heart failure or (b) heart failure hospitalization within 30 days of discharge from index myocardial infarction (see Table 1 of Appendix for more details).

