#### Secondary Endpoint

Secondary outcome measures will include a composite clinical endpoint of MACCE at 30 days follow-up, defined as (i) all-cause mortality; (ii) non-fatal myocardial infarction; (iii) transient ischaemic attack or stroke; and (iv) heart failure with or without hospitalization (see Table 1 of Appendix for more details).

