### Sample Size Determination

In a recent audit of STEMI patients across several participating sub-Saharan African hospitals, we found an all-cause mortality rate of 14% and an 18% cumulative risk of readmission with post-MI heart failure requiring in-hospital treatment at 30 days. We have based our power calculations on these recent audit data, using a primary combined event rate of 30%. We have estimated the effect size to be a 25% relative risk reduction in the 30-day event rate of all-cause death and heart failure hospitalization. We selected a 25% reduction as this effect size would be clinically meaningful and achievable for such a high-risk population. To demonstrate a 25% reduction in the primary composite endpoint, we will need to recruit 1078 STEMI patients in total to achieve 80% power, at the 5% significance level. Therefore, allowing for a conservative 10% drop-out rate at 30 days, we intend to recruit 1200 STEMI patients across the 20 recruiting centres over the 24-month recruitment period. The sample size does not include participants recruited into the observational arm of the study.

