### Statistical Analysis

All efficacy endpoints will be analysed according to the intention-to-treat principle. The primary analysis will be a comparison of all-cause death and post-MI heart failure hospitalization event rates at 30 days after randomization between the RIC and sham control arms in all randomized STEMI participants. Differences in means among the randomized groups will be analysed using the analysis of variance (ANOVA) test and, if required, the Turkey post hoc test, and differences in proportions using the χtest, or Fisher exact test, as appropriate. Follow-up will be measured from date of randomization until date of occurrence of the composite event (death or heart failure for primary analysis, and death, non-fatal MI, transient ischaemic attack or stroke, or HF with or without hospitalization for the secondary analysis) or end of the study. The primary outcomes will also be analysed in prespecified subgroups defined in our statistical analysis plan. Survival curves of study groups will be compared using the Kaplan-Meier method, and significance will be assessed using the Log-rank test. Cox proportional hazards regression models will be fitted to identify factors associated with the hazard of occurrence of the composite event. Strength of association will be expressed as a hazard ratio, with 95% confidence intervals and Wald test *p* value. All tests will be two-sided, and a *p* value < 0.05 will be considered significant. The Stata (TX, USA) statistical software will be used for data analysis.

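### Table 1's only definition of non-fatal MI does not fit the 30-day MACCE endpoint: it stops at 28 days from admission and ties the first troponin to a re-admission

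*Protocol article*

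**What the plan says.** The Secondary Endpoint section of the protocol article names "a composite clinical endpoint of MACCE at 30 days follow-up". Non-fatal MI is one of its four components. It has no time window of its own there, and the reader is sent to Table 1 of the Appendix for details.

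Table 1 has a single row for non-fatal MI: "Acute re-infarction MI that occurs in the first 28 days after the index admission for STEMI". Three numbered criteria follow: recurrent ischaemic symptoms, new ST deviation in at least two contiguous leads, and a troponin rise of at least 20% between "an immediate cTn value taken at re-admission and a subsequent cTn value taken 3–6 h later", exceeding the 99th percentile limit. The row does not say whether all three must be met.

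The Statistical Analysis section sets a different time origin: "Follow-up will be measured from date of randomization until date of occurrence of the composite event".

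Heart failure, by contrast, is split by setting in the Primary Endpoint section: "a) pre-discharge (in-hospital) heart failure or (b) heart failure hospitalization within 30 days of discharge from index myocardial infarction". Table 1 likewise has separate rows for pre-discharge heart failure and for heart failure hospitalization.

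**The concern.** A component definition should cover the same period and the same settings as the composite it feeds. This one appears to fail on both counts. Its window is shorter than the endpoint's and starts at another point. Its biomarker criterion is worded for a patient who has left hospital and returned, while its own opening line starts the window at the index admission.

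At stake is the ascertainment of one MACCE component. The Trial Intervention section has RIC or sham given at recruitment and on each of the next two days. On the literal wording, a patient who is still in the index stay on those days could not register a re-infarction. There is also a consistency problem: the trial runs at 20 sites in four countries, and an internally conflicting row invites different local readings.

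**Working it through.** **Inputs.** MACCE horizon: 30 days (Secondary Endpoint). Time origin: randomization (Statistical Analysis). MI window: 28 days from index admission (Table 1). First troponin: at re-admission (Table 1). Length of index stay, MI rate and MI timing: not given anywhere in the article.

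**Step 1: the plan's own figure, to see whether it is touched.** The only relevant computed figure is the sample size for the primary endpoint: 30% against 22.5% (a 25% relative reduction), two-sided 5%, 80% power, 1:1 allocation.

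- Pooled variance: n per arm = [1.96·√(2·0.2625·0.7375) + 0.8416·√(0.30·0.70 + 0.225·0.775)]² / 0.075² = 539.1, rounded up to 540, so 1080 in total.
- Unpooled variance: 537 per arm, 1074 in total.
- The stated 1078 lies between the two, and power with 539 per arm is 80.0%.
- With 10% drop-out: 1078 / 0.90 = 1197.8, rounded up to 1198, against the stated 1200.

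The figure reproduces. MI is not part of the primary endpoint, so nothing below changes it.

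**Step 2: the window.** Let d be the days from index admission to randomization, d ≥ 0. Counted from admission, the MI window closes at day 28 and the MACCE window at day d + 30.

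- Uncovered time = (d + 30) − 28 = 2 + d days.
- Share of the 30-day window = (2 + d)/30. At d = 0 this is 2/30 = 6.7%, the minimum.
- Illustration, assuming admission after onset and randomization within 24 h of onset, so that d is below 1 day: the share stays below 3/30 = 10%.

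**Step 3: the troponin criterion.** The possible readings of the row, side by side:

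| Reading of the row | Re-infarction during the index stay | Days 29–30 |
|---|---|---|
| Window from admission, all three criteria required, literal wording | Inside the window, but has no re-admission sample, so does not qualify | Not covered |
| Window from admission, re-admission understood as the moment of recurrence | Qualifies | Not covered |
| Window from admission, not all criteria required | Undetermined: the row does not say how many suffice | Not covered |
| Window from discharge | Excluded by the window itself | Covered if discharge is at least 2 days after randomization (2 + 28 = 30) |

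No reading makes the row agree with the 30-day endpoint in both setting and time.

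**Step 4: what the composite loses.** Let u be the patients with an uncounted MI, and v those among them who also die, have a TIA or stroke, or have heart failure within the follow-up. MACCE loses u − v patients, not u. The v patients still count, although a time-to-event analysis may date their event later. Neither u nor v can be derived from the article.

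**The case against.** **A reader might infer that every re-infarction before discharge is lost.** The text does not establish that. The row never says that all three criteria are needed. Its opening line includes the index stay, which suggests that in-hospital events were meant to count and that one word in the third criterion was badly chosen. Adjudicators may well read it that way. This stands: the defect is a conflict within the row, not a demonstrated exclusion. But a definition that works only when its wording is set aside still needs correcting, and a numbered list introduced as the definition reads most naturally as joint criteria.

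**A reader might also turn the index stay into a percentage.** An assumed stay of 5 to 10 days would be 5/30 = 17% to 10/30 = 33% of the window. The article gives no length of stay, and this would be a share of calendar time, not of events. It would be the share of MIs lost only under a constant hazard, which the article gives no ground to assume.

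**The full protocol or the cited definitions may settle the matter.** They are not shown, so nothing can be said about what sites actually do. The point is not about missing detail, however: the article prints a definition, and that definition conflicts with the endpoint printed beside it.

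**Both arms use the same rule.** Patients, treating clinicians and investigators are blinded, and no mechanism for a differential loss is apparent. This stands. It would go too far to say that the secondary result would be wrong; the expected consequence is fewer events and less precision.

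**Conclusion.** The point holds as a conflict between the MI definition and the endpoint it serves. It should be corrected, but it is confined to one component of the secondary composite.

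- **Certain from the text:** the definition ends before the endpoint does. At least 2 of 30 days (6.7% of the window) are uncovered, more by whatever time passes between admission and randomization. This rests on counting the 28 days from admission, as written.
- **Conditional:** in-hospital re-infarctions fail to qualify if the troponin criterion is taken literally and all three criteria are required. Otherwise their status depends on how each site or adjudicator resolves the wording.
- **Effect:** under-counting of non-fatal MI, probably similar in both arms. The loss of events and precision in MACCE is limited to patients whose only MACCE event is the uncounted MI. The number cannot be computed from the article.
- **Unaffected:** the primary endpoint, the 1078 evaluable patients and the 1200 to be recruited.

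**What to change.** Rewrite the non-fatal MI row of Table 1 in three respects:

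1. Define the first troponin as the one taken at onset of the suspected recurrent event, whether the patient is still in hospital or is being re-admitted; keep the second sample 3–6 h later and the rise already specified.
2. State that criteria I to III are all required.
3. Count non-fatal MI from randomization through day 30, on the same clock as the other MACCE components, in place of 28 days from index admission.

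The cost is one table row. The pair of troponin values is the one the definition already uses, and neither the sample size nor the primary analysis changes. The change should be made before any unblinded analysis, and any suspected re-infarction already classified under the present wording should be looked at again.

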## Abbreviations

AMI: Acute myocardial infarction
HF: Heart failure
MACCE: Major adverse cardiac and cerebrovascular events
MI: Myocardial infarction
PCI: Percutaneous coronary intervention
PPCI: Primary percutaneous coronary intervention
RCT: Randomized control trial
RIC: Remote ischaemic conditioning
SSA: Sub-Saharan Africa
STEMI: ST elevation myocardial infarction
cTn: Troponin
